**Figure 1 fig1:**
[figure not shown]
CONSORT flow diagram.

**Table 2 tab2:** Schedule of enrolment, interventions and assessments (SPIRIT 2025).

Timepoint	Enrolment	Intervention period	Follow-up	Close-out
	Time I 24–30 weeks of gestation	24–34 weeks of gestation	Time II 34–37 weeks of gestation	Time III ≥6 weeks after delivery
Enrolment				
Eligibility screening	X			
Informed consent	X			
Randomisation	X			
Intervention				
Psychoeducational programme (Sessions 1–6)	X	X → → → X		
Standard antenatal care + booklet	X	X → → → X	X	X
Assessments				
Sociodemographic and clinical data (Part A)	X			
PRAQ-R2 (primary outcome)	X		X	
PHQ-4	X			X
PTSD-8	X			
MSPSS	X			X
IIFAS	X			
PPQ-II				X
BSS-R				X
Obstetric outcomes (Part B)				X

PP, postpartum; PRAQ-R2, Pregnancy-related anxiety questionnaire-revised 2; PHQ-4, Patient health questionnaire-4; PTSD-8, Post-traumatic stress disorder questionnaire; MSPSS, Multidimensional scale of perceived social support; IIFAS, Iowa infant feeding attitude scale; PPQ-II, Perinatal post-traumatic stress disorder questionnaire-II; BSS-R, Birth satisfaction scale-revised.

### Sample characteristics and size

2.9

Sample size planning was informed by the Polish validation study of the PRAQ-R2, from which an anticipated 10% reduction in the mean score (3.27 points) and variability estimates for repeated measurements were derived. In this two-group randomised trial, the primary comparison will be the between-group difference in post-intervention PRAQ-R2 adjusted for baseline score, analysed using a two-sided significance level (*α*) of 0.05. Based on these assumptions, G*Power 3.1 indicated a minimum of 31 participants per group to achieve 80% statistical power. It should be noted that no MCID has been established for the PRAQ-R2 (26, 38). The 3.27-point planning assumption was derived from 10% of the Polish normative mean and additionally verified against distribution-based criteria: the anticipated difference approximates 0.5 SD of the total score [SD ≈ 8.56; (38)], a widely accepted proxy for minimal important difference in the absence of anchor-based estimates. This limitation is acknowledged; the present trial will contribute effect size data to inform future MCID derivation.

Because this is the first evaluation of an intensive, individually delivered midwife-led psychoeducational intervention in this setting, the final recruitment target of 74 women (37 per group) was retained as a pragmatic sample size balancing methodological considerations and intervention deliverability. The study is intended to provide an initial estimate of treatment effect and variance, and to inform the design of a future larger trial. An additional 20% was incorporated into the recruitment target to account for anticipated dropout, loss to follow-up, and incomplete outcome data (52, 53).

To achieve this, approximately 500 women will be screened in the second trimester to identify the eligible cohort with elevated PRAQ-R2 scores. This estimate reflects the expected prevalence of elevated PrA in the target population—a Polish pilot study found that approximately 56% of low-risk pregnant women scored ≥30 points on the PRAQ-R2 (26), combined with additional attrition anticipated from non-response, incomplete questionnaire completion, failure to meet remaining eligibility criteria, and non-consent prior to randomisation. Sample size planning was performed using G*Power 3.1.

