#### Inclusion criteria

2.4.1

Women will be eligible for inclusion if they meet all of the following criteria: are at least 18 years of age, have a singleton pregnancy, are between 24 and 30 weeks of gestation at the time of recruitment, are fluent in Polish, are not receiving care exclusively at a private maternity centre, and score ≥30 points on the PRAQ-R2. Following a review of PRAQ-R2 score distributions across international validation samples—in which mean total scores ranged from approximately 22 points (SD 6.7) in a German third-trimester sample (44) to a median of 27 points (IQR 22–32) in a Chinese sample (45) and in light of Polish normative data reporting a mean score of approximately 31 points (38), this threshold was adopted for this study. It was established in a Polish single-centre pilot study and was associated with longer labour stages and higher rates of instrumental or emergency caesarean delivery (38). It is acknowledged that this cut-off captures women with elevated but potentially sub-clinical anxiety; however, given the absence of a universally validated diagnostic threshold for the PRAQ-R2 and given that most international adaptations recommend using the scale as a continuous measure (25, 45), this pragmatic threshold reflects the best available evidence in the Polish perinatal context.

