The selection of midwives to deliver the intervention is deliberate and holds particular significance in the Polish context. The Polish perinatal care system is characterised by a high degree of medicalisation and fragmentation, which often leaves women feeling disempowered regarding the course of their pregnancy and childbirth, thereby intensifying their anxiety. Midwives, owing to their specialised knowledge of physiological pregnancy and childbirth, are ideally positioned to provide continuity of care, woman-centred communication, and support that does not pathologize natural processes. Training midwives in structured psychoeducational techniques—without requiring advanced psychotherapeutic qualifications—enhances the intervention’s scalability and potential for integration into standard prenatal care pathways. This approach aligns with the guidelines proposed by the World Health Organization (WHO), which recommend non-pharmacological interventions to reduce unnecessary caesarean sections, particularly through addressing maternal anxiety (29).

This approach is further validated by recent evidence from Padilla et al., who demonstrated that online group prenatal education delivered by midwives significantly reduced fear of childbirth in women with high levels of fear (mean difference = 22.74 points, *p* < 0.001). Their intervention—based on self-care deficit theory and consisting of five weekly videoconferencing sessions—also showed trends towards improved obstetric outcomes, including higher rates of spontaneous labour onset (65). Importantly, this was among the first midwife-led trials to evaluate a comprehensive intervention spanning both prenatal and intrapartum periods, demonstrating the feasibility and effectiveness of midwife-delivered psychoeducational programmes in routine prenatal care settings. It should be noted that the effect size reported by Padilla et al. is not directly comparable to the effect estimate used in the present power calculation, as the two studies differ in measurement instruments, intervention format, and comparison conditions. The present trial was powered based on Polish normative PRAQ-R2 data, adopting a conservative estimate to ensure robustness of the sample size calculation.

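### The claim that 31 women per group give 80% power cannot be reproduced from the printed figures, and 37 per group does not keep 31 after 20% loss

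*Protocol article*

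**What the plan says.** Section 2.9 of the protocol article takes as its planning effect "an anticipated 10% reduction in the mean score (3.27 points" and says that variability estimates for repeated measurements came from the Polish validation study. It prints neither a correlation nor a residual SD. The primary comparison is the post-intervention group difference adjusted for baseline, "analysed using a two-sided significance level (*α*) of 0.05". The stated result is: "Based on these assumptions, G*Power 3.1 indicated a minimum of 31 participants per group to achieve 80% statistical power".

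The section then checks the effect against a distribution-based criterion, saying that "the anticipated difference approximates 0.5 SD of the total score [SD ≈ 8.56; (38" and citing a different source from the validation study. It sets the target at 74 women (37 per group), which it calls pragmatic, and adds: "An additional 20% was incorporated into the recruitment target to account for anticipated dropout, loss to follow-up, and incomplete outcome data".

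Section 2.14 confirms ANCOVA with baseline PRAQ-R2 as covariate and says that multiple imputation is not planned. The Discussion says the trial was powered on Polish normative data, "adopting a conservative estimate to ensure robustness of the sample size calculation".

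**The concern.** A reader who puts the printed difference and the printed SD into a two-group calculation comes nowhere near 31 per group. The gap closes only with a strong baseline to follow-up correlation, and none is given. The one check the section offers on its effect size fails, and the dropout allowance does not protect the minimum that it was meant to protect.

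This bears on how the result will be read. The Discussion says that a non-significant result would suggest that the programme format may be insufficient and would caution against large-scale implementation. That reading is reasonable only if the trial had a good chance of detecting 3.27 points, and the 80% figure is the only assurance of that.

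**Working it through.** **Inputs.** From section 2.9: difference 3.27 points; SD 8.56; two-sided 5%; 80% power; 31 per group; 20% allowance; target 37 per group. From section 2.2: 1:1 allocation. From section 2.14: ANCOVA on baseline, no multiple imputation. From section 2.4.1: entry at PRAQ-R2 of 30 or more. The correlation r is not given, so it is varied.

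**1. Attempt to reproduce 31, unadjusted.** d = 3.27/8.56 = 0.382. Normal approximation: n = 2 × (1.960 + 0.842)² × (8.56/3.27)² = 107.6, so 108 per group; the exact noncentral t gives 109. Power with 31 per group is 32%.

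**2. With baseline adjustment.** Residual SD = 8.56 × √(1 − r²), with one further degree of freedom lost for the covariate. Here r is the correlation in the unselected population to which SD 8.56 belongs.

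| r (unselected) | Residual SD | n per group for 80% | Power at 31 per group |
|---|---|---|---|
| 0.5 | 7.4 | 82 | 40% |
| 0.7 | 6.1 | 56 | 54% |
| 0.8 | 5.1 | 40 | 69% |
| 0.85 | 4.5 | 31 | 80% |

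Solving for n = 31: √(1 − 31/107.6) = 0.844 by the normal approximation, 0.849 by the exact t. The residual SD is then 8.56 × √(1 − 0.849²) = 4.52.

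**3. What that means among enrolled women.** Selection on baseline narrows the baseline range but, under a linear model, leaves the residual SD unchanged. Assume a normal baseline with mean 31 and SD 8.56, cut at 30. The enrolled baseline SD is about 5.34, and the required correlation among enrolled women is 0.849 × 5.34 / √((0.849 × 5.34)² + 4.52²) = 0.71. The same residual SD of about 4.5 therefore reads as r = 0.85 unselected or r = 0.71 enrolled.

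**4. The 0.5 SD check.** 0.5 × 8.56 = 4.28, not 3.27. For 3.27 to be 0.5 SD, the SD would have to be 3.27/0.5 = 6.54. Even a true d of 0.5 needs 64 per group unadjusted, or r of about 0.72 to come down to 31.

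**5. The dropout allowance.** 31 × 1.2 = 37.2, which matches the target of 37. But 37 × 0.8 = 29.6, below 31. The target tolerates at most 1 − 31/37 = 16.2% loss. Keeping 31 after 20% loss needs 31/0.8 = 38.75, so 39 per group. As no imputation is planned, a woman without a Time II score leaves the primary ANCOVA.

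**6. Power for 3.27 points with 30 analysable per group.**

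| Residual SD | Power |
|---|---|
| 7.4 | 39% |
| 6.1 | 53% |
| 5.1 | 68% |
| 4.5 | 79% |

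The difference detectable with 80% power at 30 per group is about 5.5 points at residual SD 7.4 and about 4.5 points at 6.1.

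**The case against.** The strongest reply is that SD 8.56 may never have entered G*Power. Section 2.9 attributes the planning variability to the validation study and cites 8.56 from another source, only as a check. This stands. A reader might infer that the design is shown to lack 80% power, but the documents do not support that: a residual SD near 4.5 would deliver it, and they neither state nor exclude that value.

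A second reply is that entry at 30 or more changes the picture. It does, which is why power must not be quoted by pairing SD 8.56 with a correlation observed among enrolled women. Under the normal model in step 3, an enrolled r of 0.5 to 0.7 gives about 51% to 77% power at 30 per group, clearly more than the same r values give if read as unselected (39% to 53%). The selection effect makes the 80% claim less remote but does not supply the missing figure.

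Third, section 2.9 calls 74 women pragmatic and the trial a source of initial estimates, and nowhere calls the calculation sufficient. That softens the consequence, but the 80% statement remains as a formal result.

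Two further inferences should be resisted. One is that a within-group paired test was used by mistake. Such a test does give 31 at r of about 0.73, but that r is found by solving for 31, and a repeated-measures interaction also reaches a total of 62 at r of about 0.45. The method used cannot be known from the article. The other is that the means conflict: 3.27 implies a mean of 32.7, while section 2.4.1 cites "Polish normative data reporting a mean score of approximately 31 points". The two figures are attributed to different studies.

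Nor is this detail merely deferred to another document. The article says that the full protocol and analysis plan are published within it, and the point concerns a stated result, not an omission.

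**Conclusion.** The concern holds as a failure to reproduce: the printed figures do not support 80% power with 31 per group. They would require a residual SD of about 4.5 points (r of about 0.85 unselected, or about 0.71 among enrolled women under a normal model with mean 31), and the article states no such value. It does not hold as proof that the power is below 80%, because the G*Power inputs are unknown.

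Two parts need no assumption about those inputs. The 0.5 SD remark is wrong (0.38 SD), and 37 per group with the planned 20% loss leaves about 30, short of the stated minimum. The second is small on its own: at a residual SD of 4.5, power at 30 per group is still 79%. The unstated residual SD is what matters, since power for 3.27 points ranges from 39% to 79% over residual SDs of 7.4 to 4.5. Describing the estimate as conservative has no support in the article.

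**What to change.** Keep 74 women and amend the text as follows.

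- In section 2.9, rerun the calculation for the planned two-group ANCOVA at about 30 analysable per group. State the test family and the residual SD, or the SD and correlation labelled as unselected or enrolled, with the source. Replace the 80% claim with the result.
- If no source supports a residual SD near 4.5, print the range: about 39%, 53%, 68% and 79% power for 3.27 points at residual SDs of 7.4, 6.1, 5.1 and 4.5, and 80% power for about 5.5 points (residual SD 7.4) or 4.5 points (residual SD 6.1).
- Correct the distribution-based check to about 0.38 SD, and state that 37 per group leaves about 30 after 20% loss.
- In the Discussion, delete the words on a conservative estimate and robustness.
- Present the primary result as an estimate with its 95% confidence interval, so that a non-significant result is not read as evidence of no effect.

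The cost is wording only, with no extra participants and no change to the primary model. The downside is that the stated power will look less favourable unless a source for the small residual SD is found.

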### Recruitment

2.10

Recruitment will be conducted by research midwives across three settings: antenatal clinics and outpatient departments, Lamaze classes, and via targeted advertisements on social media platforms and parenting forums. A convenience sampling approach across multiple recruitment settings will be used, followed by eligibility screening and random allocation among eligible participants.

Women expressing interest will receive a link to the study information sheet and the LimeSurvey platform. After reviewing the information and providing electronic informed consent, participants will complete the baseline assessment including the PRAQ-R2 and sociodemographic questionnaire. The LimeSurvey system has been configured so that the final PRAQ-R2 score is visible exclusively to the research team and not to participants, preventing unnecessary distress and allowing for objective eligibility assessment. Women whose PRAQ-R2 score meets or exceeds the predefined threshold will be contacted by telephone within 1 week to confirm willingness to participate and verify inclusion criteria. Women who provide consent at this stage will be formally enrolled in the trial.

To monitor recruitment balance across settings, the source of recruitment will be recorded for each participant at enrolment. Descriptive analyses will examine potential differences in baseline characteristics between women recruited through different channels, and recruitment source will be included as a covariate in sensitivity analyses if meaningful imbalances are identified.

### Randomisation and blinding

2.11

Allocation to study groups at a 1:1 ratio will be performed using block randomisation with variable block sizes, computer-generated by a researcher not involved in recruitment. Allocation concealment will be ensured through sequentially numbered, opaque, sealed envelopes. The recruiting midwife will open the next consecutive envelope only after obtaining the participant’s final informed consent. Blinding of participants and intervention-delivering midwives is not feasible given the nature of the psychoeducational programme, consistent with standard practice in behavioural RCTs. Since all outcome questionnaires are self-completed via a secure online platform, no assessor is present at any data collection time point, which substantially mitigates assessment bias. The researcher responsible for data management and the data analyst will both be blinded to group allocation throughout the analysis phase, using coded group labels. Unblinding will only occur if authorised by the principal investigator for safety or ethical reasons and will be formally documented.

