### Trial setting

2.3

This nationwide, multi-centre study will be conducted across Poland. Participants will be recruited from public antenatal clinics and outpatient departments, childbirth education schools, and through online platforms such as social media and parenting forums. Private maternity centres are excluded from recruitment to minimise selection bias. This multi-channel strategy ensures broad geographic reach and sample diversity. Intervention sessions will be delivered either in person at a location convenient for the participant or remotely via secure video conferencing. The study will be coordinated by the research team at the Medical University of Gdańsk.

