#### Exclusion criteria

2.4.2

Women will be excluded from the study if they meet any of the following criteria: absolute or strong medical indication for caesarean delivery (e.g., placenta praevia); multiple pregnancy; diagnosis of a severe psychiatric disorder (e.g., active psychosis, schizophrenia, bipolar disorder) that could interfere with informed consent or study participation; current pharmacological treatment for anxiety or depression, regardless of symptom severity, as concomitant psychotropic medication may confound the assessment of intervention effects; concurrent participation in another structured psychological intervention; or inability to commit to the study schedule.

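### The recruiting midwife opens the allocation envelopes herself in an open trial, with no independent release once eligibility is settled; central release would be a cheap improvement

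*Protocol article*

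**What the plan says.** **Sequence and concealment (2.11 Randomisation and blinding).** The list is made by "block randomisation with variable block sizes, computer-generated by a researcher not involved in recruitment". "Allocation concealment will be ensured through sequentially numbered, opaque, sealed envelopes". Release is in the recruiter's hands: "The recruiting midwife will open the next consecutive envelope only after obtaining the participant’s final informed consent".

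**Blinding (2.11).** "Blinding of participants and intervention-delivering midwives is not feasible given the nature of the psychoeducational programme". The data manager and the analyst are blinded, and outcomes are self-completed online.

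**Recruitment (2.10) and setting (2.3).** "Recruitment will be conducted by research midwives across three settings". "This nationwide, multi-centre study will be conducted across Poland". Consent is electronic. Women at or above the PRAQ-R2 threshold "will be contacted by telephone within 1 week to confirm willingness to participate and verify inclusion criteria". Those who then consent are enrolled. The research team can see the score before that point.

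**Exclusion criteria (2.4.2).** The last criterion listed is "inability to commit to the study schedule".

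**Analysis (2.14).** The primary model is ANCOVA adjusted for baseline PRAQ-R2. The section also says that stratification variables used in the randomisation will enter the model, but 2.11 describes no stratification.

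**The concern.** Concealment should prevent anyone who influences entry from acting on knowledge, or a good guess, of the next assignment. In this plan the person who recruits also releases the assignment. She learns every allocation she opens. The steps just before opening leave room for discretion: whether a woman is willing, and whether she can commit to the schedule. Because enrolment is by telephone and electronic consent, the plan describes nothing that would show afterwards whether eligibility was settled before the envelope was opened.

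If a recruiter did anticipate an assignment, she could delay a call, encourage a woman, or judge that she cannot keep to the schedule. Motivation and expected engagement could then differ between the arms at entry. Adjusting for baseline PRAQ-R2 deals with selection on the score but not with those traits, and blinding the analyst cannot repair selection at entry. The primary outcome is rated by unblinded women, so secure concealment carries much of the weight in this design.

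**Working it through.** The article gives no predictability figure, so there is nothing of the plan's own to reproduce. The check asks how well a recruiter could guess under the stated design, across what is left open.

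**Inputs from the protocol article:** 1:1 allocation in blocks of variable size (2.11); 74 women (2.9); more than one recruiting midwife (2.10).

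**Assumptions, because not stated:** block sizes from 2 to 10; one to ten recruiters; one shared list or a separate list per recruiter.

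**Guessing rule.** Guess the arm with fewer assignments so far; toss a coin when they are level.

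**1. Every earlier assignment on the list is known, fixed block size 2m.** The expected share of correct guesses is

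[m + 2^(2m−1)/C(2m, m) − 1/2] / (2m)

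- Size 2: (1 + 2/2 − 0.5)/2 = 75.0%
- Size 4: (2 + 8/6 − 0.5)/4 = 70.8%
- Size 6: (3 + 32/20 − 0.5)/6 = 68.3%
- Size 8: (4 + 128/70 − 0.5)/8 = 66.6%
- Size 10: (5 + 512/252 − 0.5)/10 = 65.3%

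**2. Variable block sizes, 74 assignments, simulated (4,000 runs per scenario).** In the shared-list columns each woman is assigned to a recruiter at random, and each recruiter knows only her own cases.

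| Block sizes | One observer of the whole list | Separate list for each of 4 recruiters | Shared list, 2 recruiters | Shared list, 5 recruiters | Shared list, 10 recruiters |
|---|---|---|---|---|---|
| 2, 4 | 72.1% | 71.4% | 53.9% | 51.7% | 51.3% |
| 2, 4, 6 | 70.1% | 69.2% | 53.9% | 51.9% | 51.2% |
| 4, 6 | 69.2% | 68.1% | 53.8% | 51.8% | 51.1% |
| 4, 6, 8 | 68.0% | 66.9% | 53.8% | 51.9% | 51.3% |
| 6, 8, 10 | 66.2% | 64.9% | 53.7% | 51.8% | 51.2% |

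Varying the block size does not by itself defeat this rule. What matters most is whether the recruiter knows the earlier assignments on her list.

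**3. Certainty rather than a guess.** If the block size is known, the share of assignments fully determined by earlier ones is 1/(m + 1): 33% for size 4, 25% for size 6, 20% for size 8. Variable blocks are meant to prevent this.

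**4. Room for selection before allocation (2.9).** About 500 women are to be screened and about 56% are expected to score ≥30: 500 × 0.56 = 280 for 74 places. The article attributes the difference to non-response, incomplete questionnaires, other criteria and non-consent. Only part of it can fall at the telephone step, and the article does not say how much.

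**The case against.** The strongest defence is that this is a recognised method with real safeguards. Someone outside recruitment makes the list, block sizes vary, the envelopes are opaque, sealed and numbered, and they are opened only after final consent. All of that stands. Details such as block sizes and who holds the envelopes are commonly left out of an article, and their absence is not counted as a fault here.

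Four stronger readings are tempting, and the document does not support them.

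- **That assignments can be seen in advance.** Section 2.11 says the opposite. Early sight would need tampering or a breach of the procedure.
- **That the next assignment can be guessed about 70% of the time.** That needs small blocks and a recruiter who knows every earlier assignment on her list. With one shared list and five recruiters who know only their own cases, the rate is about 52%.
- **That each recruiter has her own set of envelopes, and that the midwife who opens the envelope also made the call.** Section 2.10 does not name the caller, and nothing says the envelopes are divided. A single run held at the coordinating institution fits the text equally well.
- **That the bias is 0.4 to 1.2 points.** This uses bias = (2p − 1) × shift with p = 0.70 and an assumed shift of 1 to 3 points, giving 12% to 37% of the planned 3.27. The shift has no source in the document, and every guess must be acted on in the same direction. At p = 0.52 the same formula gives 0.04 to 0.12 points, or 1% to 4%.

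The Discussion also says that reasons for screening refusal will be recorded where possible, which partly covers a log of women not randomised. What survives the defence is narrower: the recruiter alone releases the assignment, and no independent check on the order of events is described.

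**Conclusion.** The point holds as a weakness of a stated design choice, not as an error in the plan. Section 2.11 gives release of the allocation to the recruiting midwife, in a trial open to participants and deliverers, directly after steps that involve judgement. No eligibility lock or independent release is described, so concealment depends on her compliance alone.

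The possible guess rate runs from about 51% to 75%. The lower end assumes one shared list and ten recruiters who know only their own cases. The upper end assumes blocks of 2 and full knowledge of earlier assignments. The document does not place the trial within that range, so no single guess rate and no size of bias should be attached to it. A better method is available at little cost and has to be in place before or early in recruitment, because selection at entry cannot be undone in the analysis.

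**What to change.** Amend 2.11 as follows.

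- The researcher who generates the list and is outside recruitment holds the sequence centrally, or it sits in a locked allocation table in LimeSurvey.
- Each assignment is released for a study ID only after final consent and every eligibility answer, including the schedule criterion, are recorded with a time stamp.
- One sequence is shared across recruiters, within strata if there are any. Sections 2.11 and 2.14 must be reconciled on whether the randomisation is stratified.
- Every woman scoring ≥30 who was telephoned but not randomised is logged with the reason.

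Central release chiefly removes the dependence on how recruiters handle envelopes. It lowers guessing from past assignments only where several recruiters share the sequence and know only their own cases; with one recruiter who sees every allocation, the rates for a single observer would remain.

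The cost is a short amendment and a short delay between consent and allocation. It uses a researcher and a platform already in the plan and needs no extra participants.
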